### Data collection and management

A case report form (CRF) will be filled in for each participant before intervention. The collection of baseline data, along with primary and secondary outcomes, will be recorded completely in CRF. Each participant (corresponding to a CRF) will be assigned a specific number by which intervention and follow-up will be performed. Using ResMan, an Internet-based Electronic Data Capture (EDC) tool, all information will be kept independently as double copies in a computer. The data files will be locked after a blind audit and confirmed to be reliable. The CRF shall be owned by the principal investigator and shall not be provided to any third party in any form without the written approval of the principal investigator, who will oversee all of the final trial data. A follow-up registration form will be given to all patients to encourage retention. A researcher will collect the reason for loss, survival condition, and recent outcome assessment for participants who lose from intervention. The original paper files will be kept in the filing cabinet of the sponsoring organization and clinical data will be kept for 5 years.

### Quality control

A data monitoring committee (DMC), which will consist of neurosurgery experts and statisticians, will be established; this will be independent of the sponsor and trial investigator. Periodically, the DMC will assess the progress of the clinical trials, safety data, and important efficacy data. The DMC will also perform an interim evaluation and advise if the trial should be modified or discontinued based on the results of the interim evaluation.

In the course of the study, an inspector will verify the accuracy and completeness of the CRFs and compare them with the source documents. Inspecting must ensure that the subject’s dose changes, treatment changes, adverse events, combined medications, missed visits, and examination omissions are noted in the CRFs. Additionally, they must confirm that the withdrawals and missed visits of the selected subjects have been recorded and explained in the CRFs. As well, the inspector will notify the researcher of the errors, omissions, or unclear handwriting in CRFs and ensure that correction, addition, or deletion is carried out by the researcher or authorized person. The modification must be documented in writing, if necessary. The inspector will promptly inform the principal after each supervision and inspection.

### Statistical analysis

We will use SPSS 23.0 statistical software for Windows to perform statistical analysis. To ensure the reliability of our conclusions, we plan to use intention-to-treat (ITT) analysis as the main form of analysis.

#### Baseline description

Means ± standard deviation (SD) will be used to describe quantitative data that are normally distributed; medians and interquartile ranges (IQRs) will be used to describe non-normal distribution data. The constituent ratio or relative ratio will be used to describe the count data.

#### Comparison of baseline data

*T*-tests will be performed for quantitative data that are normally distributed. A non-parametric test will be used for quantitative data that is not normally distributed. The chi-squared (*χ*^2^) test will be used for counting data. A two-sided *P* value < 0.05 will be considered to be statically significant.

#### Comparison of therapeutic efficacy

A Kaplan–Meier survival analysis with a Log-rank test will be used to compare survival data (PFS and OS) between the two arms. Confounding factors, including demographic data, medical history of drug use prior to intervention, epileptic seizure, and the molecular prognostic markers, will be analyzed by Cox proportion hazards regression analysis. Results will be expressed as hazard ratios (HRs) and 95% confidence intervals (CIs). Furthermore, the KPS and the ORR (ranked data) of the two arms will be compared by Wilcoxon’s rank-sum test.

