Levetiracetam (LEV), as an antiepileptic drug (AED), is mainly used for the treatment of partial seizures in adults and children with epilepsy over 4 years of age. In recent years, studies have found that levetiracetam was associated with a better survival rate when used in GBM patients [12–15]. Although these observational studies provide a compelling background for investigating the effect of LEV on GBM, the limitation of these studies stems from retrospective nature, including selection and information bias. On the other side, antiepileptic drugs used asynchronously with chemotherapy might underpower the potency of the anti-tumor effect of AEDs. It is not clear how LEV improves survival in patients with GBM. The potential antitumor activity of LEV might be due to the inhibition of MGMT transcription and expression in glioblastoma cell lines by increasing p53 binding on the MGMT promoter, thus sensitizing glioblastoma cells to the alkylating agent TMZ [16]. In addition, Scicchitano et al. reported that LEV enhances the effect of TMZ on proliferation and apoptosis in GBM cancer stem cells [17]. Furthermore, a study in vitro showed that the tumor-suppressing effect and the induction of cellular senescence of LEV are further enhanced when TMZ is combined with β-galactosidase activity [18]. The combination of TMZ and LEV is expected to offer complementary benefits and thus amplify the anti-tumor effect of TMZ.

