#### Baseline evaluation: conducted within 2 weeks before the start of the trial

Demographic dataPast medical history (diagnosis and treatment)KPSHead MRIThe molecular prognostic markers: IDH status (IDH-wildtype/IDH-mutant) and MGMTp status (unmethylated/methylated)Laboratory test: complete blood counts (CBC) and liver and renal function

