### Sample size

The determination of sample size was calculated by PASS 15.0 software. Based on a previous study and clinical assumptions [26], the median OS of standard care for GBM is 14.6 months while that of the experimental group (TMZ plus LEV ) is 24 months. Statistical parameters are set as follows: one-sided log-rank testing with 80% power, the probability of obtaining a false positive with a statistical test at 0.05, and a 3-year follow-up time. Considering a potential dropout rate of 10% across both groups, it is estimated that 142 patients will need to be enrolled (71 participants per group).

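### The log-rank comparison of PFS and OS leaves out the MGMT, IDH and KPS values collected at baseline, and the seizure covariate in the Cox model has no time point

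*Protocol article*

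**What the plan says.** Under Comparison of therapeutic efficacy, a Kaplan–Meier analysis "with a Log-rank test will be used to compare survival data (PFS and OS) between the two arms". No stratum or covariate is attached to that test. Interventions describes blocked randomisation, and neither that section nor Randomization and blinding names a stratification factor.

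The same paragraph then sends a list of confounding factors to a Cox regression: demographic data, then "medical history of drug use prior to intervention, epileptic seizure, and the molecular prognostic markers". Hazard ratios with 95% confidence intervals follow.

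Baseline evaluation records KPS, past medical history and two molecular markers, "IDH status (IDH-wildtype/IDH-mutant) and MGMTp status (unmethylated/methylated"). MGMT and IDH are therefore in the Cox model but not in the log-rank test. Baseline KPS is named in neither. Seizures are not a separate item in the baseline, on-treatment or follow-up lists.

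The Background describes levetiracetam, the study drug, "as an antiepileptic drug (AED), is mainly used for the treatment of partial seizures".

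**The concern.** There are two separate issues in one paragraph of the plan.

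The first is efficiency. The protocol itself treats MGMT as a mechanism of temozolomide resistance and calls MGMT and IDH prognostic. Entry is open from KPS 50 upwards, so baseline performance status can vary widely. With no stratified randomisation and no stratified or adjusted primary test, a chance imbalance in these factors goes straight into the primary comparison, and the variation they explain is left as noise. The trial is planned at 80% power, one-sided, and its authors describe the sample as relatively small.

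The second is the seizure covariate. Only the drug history is expressly limited to the time before the intervention. If seizures after randomisation were counted, the model would condition on something the antiepileptic study drug can alter. The section on adherence and concomitant care links seizures to tumour tissue. If aggressive tumours cause both seizures and progression, conditioning on seizures ties treatment to tumour aggressiveness and can move the treatment hazard ratio even when the drug does nothing to survival.

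**Working it through.** **Design figures (Sample size section).** The inputs are "one-sided log-rank testing with 80% power", "the probability of obtaining a false positive with a statistical test at 0.05", "the median OS of standard care for GBM is 14.6 months" and "that of the experimental group (TMZ plus LEV ) is 24 months", with 36 months of follow-up, 36 months of accrual (Recruitment section) and 10% dropout.

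- Hazard ratio if survival is exponential: 14.6/24 = 0.608.
- Freedman events: (1.645 + 0.842)² × ((1 + 0.608)/(1 − 0.608))² ≈ 104.3, rounded up to 105.
- Event probability with uniform accrual over 36 months and 36 more months of follow-up: 0.913 (control) and 0.780 (experimental), mean 0.847.
- N = 105/0.8467 = 124.01, rounded up to 125. Then 125/0.9 = 138.9, so 139, or 140 in equal arms.

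The stated 142 is reproduced to within 2. It uses OS medians and no covariates, so this point does not touch the sample-size arithmetic. Evaluable patients: 142 × 0.9 ≈ 128.

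**Power with MGMT as stratum.** The documents give no MGMT effect and no methylation rate. Assumed: 128 patients, treatment hazard ratio 0.608 within MGMT strata, exponential times with an overall control median of 14.6 months, censoring uniform over 36–72 months, 45% methylated, one-sided 0.05, 10,000 replicates per row.

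| MGMT hazard ratio | Plain log-rank | Stratified log-rank | Difference (points) |
|---|---|---|---|
| 1.0 | 82.6% | 81.8% | −0.9 |
| 0.7 | 81.2% | 82.1% | +0.9 |
| 0.5 | 76.0% | 80.2% | +4.3 |
| 0.4 | 71.7% | 80.2% | +8.5 |

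(Differences are taken before rounding.) A separate simulation under the same main assumptions gave 77% against 81% at 0.5 and 73% against 81% at 0.4. If 14.6 months is instead assigned to unmethylated controls, the last two gaps are 4.1 and 6.9 points. Type I error of both tests stayed between 4.7% and 5.6%.

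**Power with MGMT and KPS in a Cox model.** Here 30% of patients were assumed to have low KPS, and 14.6 months was the control median of patients without either factor.

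| MGMT HR, KPS HR | Unadjusted | Adjusted |
|---|---|---|
| 1.0, 1.0 | 83% | 82% |
| 0.7, 1.3 | 80% | 81% |
| 0.5, 1.5 | 72% | 77% |
| 0.4, 2.0 | 67% | 77% |

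The simulation error is about 1 point.

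**Seizure covariate under the null.** The documents give no seizure rates. Assumed: the drug has no effect on survival; half the patients have aggressive tumours; aggressiveness multiplies both the seizure odds and the hazard; the drug lowers the seizure odds; a yes/no on-treatment seizure indicator enters the Cox model.

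| Aggressiveness: seizure OR, HR | Drug OR on seizures | Unadjusted HR | Seizure-adjusted HR |
|---|---|---|---|
| 2, 1.5 | 0.5 | 0.99 | 1.00 |
| 3, 2 | 0.5 | 1.01 | 1.04 |
| 3, 2 | 0.3 | 0.99 | 1.03 |
| 5, 3 | 0.3 | 1.01 | 1.09 |

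The simulation error is about 0.01. A true hazard ratio of 1.00 becomes about 1.00 to 1.09. A seizure history fixed before randomisation would cause no such bias.

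**The case against.** A reader might infer that the Cox model definitely adjusts for seizures that the study drug has changed. The text does not say so. The term stands in a list of confounders, between drug history before the intervention and markers measured at baseline. The past medical history could hold it. The rules for antiepileptic use sort patients by epilepsy before or after surgery, and with entry up to 3 months after surgery, much of that is known at randomisation. Seizures are also missing from the on-treatment and follow-up lists, so their absence from the baseline list proves nothing. Baseline history is an equally open reading. Against that, the same rules also foresee seizures during antiepileptic withdrawal, and nothing excludes them from the covariate.

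A reader might also infer that the primary result is biased. It is not: the log-rank test contains no seizure term, and an unadjusted test is valid in a randomised trial. Nor does the plan ignore MGMT and IDH, since the Cox model has them. The omission of KPS is a weak point, because the covariate list is given as inclusive and the article is a condensed document.

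The sizes rest on assumptions. The power gain needs strong prognostic effects. The hazard ratio of 0.608 comes from OS medians although PFS is primary. Valproate is planned for patients with and without epilepsy in both arms, which could shrink any difference in seizures. Any seizure bias would tend to work against levetiracetam, so it would not manufacture a benefit.

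All of this stands and limits the point. What it does not answer is that the covariate is named without a time point, and that useful baseline data are left out of the main test.

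**Conclusion.** The point holds as an efficiency improvement and a wording repair, not as an error in the primary test.

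An unstratified log-rank test gives up about 4 to 9 points of power against an MGMT-stratified one if the MGMT hazard ratio is 0.5 to 0.4. The difference is about a point either way if the effect is weak or absent. Type I error is about 5% with either test. These figures assume 128 evaluable patients, 45% methylated, exponential survival, a treatment hazard ratio of 0.608 and the protocol's one-sided 0.05.

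The seizure covariate is ambiguous. Only if it counted seizures after randomisation would the adjusted hazard ratio be at risk, by up to about 9% against levetiracetam under the null on the assumed inputs. The documents do not show that this is intended, but as written they allow it, and the choice could be made after the data are seen.

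**What to change.** Before unblinding, amend the analysis text as follows.

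- Make the primary PFS comparison, and the OS comparison, either a log-rank test stratified by MGMT status or a Cox model with treatment, MGMT, IDH, baseline KPS and age. Choose one in advance.
- Keep the plain log-rank test as a supportive analysis.
- State that only values fixed before randomisation may enter the Cox model, and replace the seizure term with seizure history before randomisation.

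The cost is a change of wording. MGMT, IDH, KPS and demographic data are already collected. Seizure history has to be taken from the past medical history or confirmed as a baseline entry. If MGMT has no prognostic effect, stratifying costs about 1 point of power. A covariate-adjusted hazard ratio is conditional on the covariates and need not equal the unadjusted one: in the MGMT and KPS simulation, a conditional 0.608 appeared as 0.63 to 0.66 unadjusted under the two stronger settings. The report should say which one is given.

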#### Safety evaluation

Incidence of adverse events (CTC-Toxicity ≥ grade3) will be expressed as the number of patients (percentage) and be analyzed by the chi-square (*χ*^2^) test.

### Reports of adverse events

Adverse events (AEs) will be assessed primarily by abnormal variations in laboratory data (including complete blood counts (CBC), liver function tests (total bilirubin level, AST, ALT), renal function tests (creatinine clearance, blood urea nitrogen), and clinical symptoms. The occurrence, severity level, management strategies, the causality related to the experimental agents, and the termination of all adverse events (AEs) will be recorded and preserved during clinical trials and follow-up. All severe adverse events (CTC-Toxicity ≥ grade3) will be reported promptly to the principal investigator and the research ethics committee (REC). The researchers and clinical trial institutions will ensure that the subjects are treated appropriately and informed truthfully of the relevant information. According to China’s Code of Quality Management for Drug Clinical Trials, researchers are responsible for the cost of dealing with adverse reactions and compensation for patients who suffer adverse reactions. Participants are not provided with specific post-trial care.

## Discussion

In the past, adjuvant chemotherapy for GBM has traditionally been performed with nitrosoureas, such as carmustine (BCNU) and lomustine (CCNU) [27, 28]. Drug resistance and side effects limit the efficacy of these drugs. PCV is a combination of procarbazine, CCBU, and vincristine based on these studies. However, studies have shown that there are no significant survival benefits associated with the use of PCV [29]. Stupp et al. [26] demonstrated in 2005 that concurrent and adjuvant TMZ therapy for 6 months significantly improved the median survival rate for patients with glioblastoma (14.6 months compared to 12.1 months). The Stupp protocol is the most effective chemotherapy to treat GBM to date.

Despite advances in chemotherapy therapy, patients with GBM who have undergone surgery are confronted by drug resistance and tumor recurrence; these factors can lead to immense physical and financial stress. Hwang et al. reported the negative results for patients with GBM in their clinical trial for LEV on the survival benefits of patients with GBM in 2022 [19], which is opposite to their observational study [30]. However, this study was limited by its single-arm design. If our results indicate that the new combination chemotherapy (TMZ plus LEV) is effective, then this clinical trial could provide high-level evidence and broad potential applications for GBM as a first-line treatment regime. Patients with GBM, especially those with TMZ resistance and those with MGMT positivity, will benefit from this new regimen by targeting multiple anti-tumor mechanisms. In China, this is the first prospective, randomized, and controlled clinical trial to investigate the efficacy of TMZ combined with LEV in patients with GBM after surgery. Additionally, we will use PFS as a primary outcome indicator and will also capture several secondary outcome parameters. These relatively objective evaluation indices will be used to evaluate the effectiveness of the new combination regimens.

The study has several limitations that need to be considered. First, while the recruited patients underwent maximum surgical resection, the extent of tumor resection remains a controversial prognostic factor due to the different tumor locations and different surgeons. There is no doubt that, in the treatment of GBM, the role of collaborative drugs cannot take precedence over surgery. Second, since there is no coherent guidance that can be referenced regarding the optimal use of LEV in patients with GBM (for example, treatment period, optimal dose, and discontinuation indicators), the administration of LEV has been a lack of evidence. Previous studies have demonstrated that LEV was generally well tolerated in epilepsy treatment without serious systemic adverse reactions [23, 31]. In the trial, LEV will be administered according to the common dose range for seizure control that has been adopted. Third, since all patients will be recruited from a single hospital, the results of the trial cannot be generalized to other ethnicities and regions. The study is also limited by its relatively small sample size.

In summary, this RCT may contribute to the development of an optimal treatment regimen to extend the survival rate of patients with GBM. Further research is needed to verify the role of LEV in improving the survival of patients with GBM and controlling epilepsy.

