### Outcomes

2.3.1 Primary outcome

The primary outcome is the PFS of patients, the time from randomization and group allocation to any recorded disease progression, and even death.

2.3.2 Secondary outcomes are as follows:
Overall survival (OS), the time from randomization and allocation to death for any reasonThe Karnofsky Performance status scale (KPS). The scale measures the levels of patient activity and medical needs. The score ranges from 100 (no signs of disease) to 0 (dead).Objective response rate (ORR) = (CR + PR)**/**total number of cases × 100%. A complete response (CR) is defined as the disappearance of all target lesions. A partial response (PR) is defined as a reduction of at least 30% in the sum of diameters of the target lesions, considering the baseline sum diameters as a reference. The ORR will be determined by MRI according to the Response Evaluation Citeria in Solid Tumors (RECIST) [20].Incidence of adverse events (AEs). Adverse events (CTC-Toxicity ≥ grade III) will be recorded and analyzed based on the Common Terminology Criteria for Adverse Events (CTC-AE) [21].

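### The named Cox covariates leave out residual tumour, although extent of resection is the protocol's first stated limitation and a post-operative baseline MRI is already planned

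*Protocol article*

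**What the plan says.** The Discussion opens its limitations with surgery: "the extent of tumor resection remains a controversial prognostic factor due to the different tumor locations and different surgeons". It then adds: "There is no doubt that, in the treatment of GBM, the role of collaborative drugs cannot take precedence over surgery".

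Under Comparison of therapeutic efficacy, the between-arm comparison is unadjusted: "A Kaplan–Meier survival analysis with a Log-rank test will be used to compare survival data (PFS and OS) between the two arms". A Cox model follows, and its covariates are given as "Confounding factors, including demographic data, medical history of drug use prior to intervention, epileptic seizure, and the molecular prognostic markers". Results are to be reported as hazard ratios with 95% confidence intervals. Neither resection nor residual tumour is named.

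The eligibility criteria require that every patient has had a maximal resection. They set no residual-tumour threshold and allow entry up to 3 months after surgery. Interventions and Randomization and blinding describe a blocked 1:1 sequence and mention no stratification.

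Head MRI and treatment history are among the baseline items ("Baseline evaluation: conducted within 2 weeks before the start of the trial"). The ORR definition under Outcomes measures response "considering the baseline sum diameters as a reference".

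**The concern.** The protocol singles out one surgical factor as a possible threat to interpretation, and then names a set of adjustment variables without it. Residual tumour can vary among enrolled patients because no threshold is set. Nothing described in the design balances it between two arms of 71.

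If the factor is prognostic, leaving it out of the Cox model has two effects. The estimated treatment hazard ratio is pulled somewhat towards 1, with a loss of power. Any chance difference in residual tumour between the arms also stays in the reported PFS and OS hazard ratios. The protocol treats the matter purely as a limitation, although its planned data allow a partial adjustment.

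**Working it through.** **Design inputs (Sample size; Recruitment and eligibility criteria).** "the median OS of standard care for GBM is 14.6 months", against 24 months in the experimental group; "one-sided log-rank testing with 80% power"; alpha 0.05; 3 years of recruitment; 3 years of follow-up; 10% dropout; 142 patients, 71 per group. These are OS inputs, because the protocol gives no PFS assumption.

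**Reproducing 142.**
- Under exponential survival, HR = 14.6/24 = 0.608.
- Freedman events = (1.645 + 0.842)² × [(1 + 0.608)/(1 − 0.608)]², which rounds up to 105.
- With 36 months of uniform accrual plus 36 months of follow-up, P(event) = 1 − [exp(−36λ) − exp(−72λ)]/(36λ). With λ = ln 2/14.6 and ln 2/24 this is 0.913 and 0.780, mean 0.8467.
- 105/0.8467 = 124.01, rounded up to 63 per arm, gives 126. Then 126/0.9 = 140, close to the stated 142.
- The proposed change does not affect this number.

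**Assumptions not in the documents.** Residual tumour is binary, with prevalence 30% or 50% and a prognostic hazard ratio of 1.3 to 2.5.

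**Cox model without and with the covariate.** 128 analysable patients (142 less 10%), treatment HR 0.608, a fixed 36 months per patient, 2,000 simulated trials per setting, one-sided 0.05:

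| Prognostic HR | Prevalence | Power without | Power with | Mean HR without | Mean HR with |
|---|---|---|---|---|---|
| 1.3 | 30% | 78.2% | 78.3% | 0.604 | 0.601 |
| 1.3 | 50% | 76.8% | 77.4% | 0.609 | 0.604 |
| 1.5 | 30% | 76.5% | 77.5% | 0.611 | 0.603 |
| 1.5 | 50% | 76.7% | 78.1% | 0.613 | 0.604 |
| 2.0 | 30% | 73.1% | 76.4% | 0.627 | 0.609 |
| 2.0 | 50% | 73.4% | 77.4% | 0.625 | 0.603 |
| 2.5 | 30% | 70.8% | 77.6% | 0.631 | 0.599 |
| 2.5 | 50% | 68.3% | 75.6% | 0.639 | 0.603 |

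The gain is 0.1–0.6 points at 1.3, 1.0–1.4 at 1.5, 3.3–4.0 at 2.0 and about 7 at 2.5. Each power figure has a simulation standard error of about √(0.77 × 0.23/2000) = 0.9 points. The two columns use the same simulated trials, so their differences are steadier than that. Power sits below 80% throughout because a fixed 36 months yields fewer events than the accrual scheme above.

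**Validity.** With no treatment effect (1,500 trials per setting), the rejection rate is 4.0–5.1% without the covariate and 4.5–5.4% with it. Both are near 5%.

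**Chance imbalance.**
- SD of the difference in prevalence between arms = √[2p(1 − p)/71] = 7.7 points at p = 0.3 and 8.4 points at p = 0.5.
- The 95% limit, 1.96 × SD, is 15.1 and 16.4 points. A gap of at least 10 points has probability 19% and 23%.
- Approximate shift in the unadjusted HR = exp[ln(prognostic HR) × gap]. At the 95% limit this is 1.040–1.044 for a prognostic HR of 1.3, 1.063–1.069 for 1.5 and 1.110–1.121 for 2.0. At a 10-point gap it is 1.027, 1.041 and 1.072.
- For scale, 128 × 0.733 (P(event) at a fixed 36 months) ≈ 94 events, so the standard error of the log HR is about 2/√94 = 0.21. The largest of these shifts, ln 1.12 = 0.11, is about half of that.

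**The case against.** Several counter-arguments have force.

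**The list is open.** The covariate list begins with the word including, and a full analysis plan may name more. Residual tumour is therefore unnamed, not excluded. This stands. The article does choose to name its adjustment variables, however, and an open list leaves the remaining choice to be made later. Naming the factor that its own limitations put first is a specific improvement.

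**The protocol does not call it a strong factor.** A reader might infer that the protocol ranks extent of resection above drug effects. It does not. It calls the factor controversial, and the sentence on precedence concerns surgery in general, which every patient has had.

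**The MRI does not give extent of resection.** A reader might infer that the baseline diameters already supply it. They do not. The scan can fall up to about 3 months after surgery and shows residual or regrown tumour, whereas extent of resection also needs the pre-operative size or the surgical record. A sum of target-lesion diameters would also miss residual disease not chosen as a target. This limits the covariate to a proxy.

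**The primary test is unaffected.** A reader might infer that the covariate would raise the power of the planned comparison. It would not: the log-rank test is unadjusted, and adding a Cox term leaves it unchanged. A stratified log-rank test would show gains of a similar size (78.9% to 79.8% at a prognostic HR of 1.5, and 75.6% to 79.0% at 2.0, with 30% prevalence, 64 per arm and 43.8 months), but that is a different change.

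**Chance imbalance is already covered by the confidence interval.** On average over randomisations this is true, and type I error confirms it. Adjustment still helps in the particular trial at hand, where the imbalance will be visible.

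**Conclusion.** The point holds in a modest form. The named Cox covariates omit any measure of residual tumour, although the limitations raise resection first, no stratification is described, and a usable baseline scan is planned. The loss is in precision and in conditional balance of the PFS and OS hazard ratios. No bias in the randomised comparison and no invalid test is shown.

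The effect is negligible to small for a weak factor and worth having for one with a prognostic hazard ratio near 2. The documents do not say which applies. The power and attenuation figures rest on OS inputs, exponential survival and a binary factor, and how far they carry over to PFS is unknown.

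**What to change.** Under Comparison of therapeutic efficacy, add one sentence: *Residual tumour on the baseline head MRI (present or absent), read without knowledge of treatment arm, will be a pre-specified covariate in the Cox models for PFS and OS.* Reading presence or absence from the scan itself, not from whether the target-lesion sum is zero, keeps non-target residual disease in the right group.

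Describe the variable as a residual-tumour proxy. In the Discussion, reword the first limitation to say that it is partly addressed by this adjustment. It should not say that extent of resection has been adjusted for. Settle both changes before unblinding.

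The cost is one sentence in the analysis section, a small edit to the Discussion, a blinded reading of a scan already planned, and one further model parameter. No new procedure is needed and the sample size does not change.
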